### Aims and hypotheses

1.1

The main objective of the project is to implement and evaluate the efficacy of a stepped online ecosystem for detecting, following, and addressing the psychosocial needs of patients with lung cancer and to compare those with usual face-to-face treatment. We aim to detect cases at risk of significant emotional distress and decrease the time to access appropriate psychosocial care when using eHealth and usual face-to-face care.

Comparisons between the two interventions will consider the effects on ameliorating the psychosocial consequences of lung cancer and its treatment on emotional distress, demoralization, QoL, and medication adherence, including consideration of the role of spirituality and patient perception of their health education. The cost-utility of each intervention will then be analyzed in terms of quality adjusted life years (QALYs), considering use of additional health services, consumption of psychotropic drugs, sick leave durations, professional salaries, and infrastructure and transportation costs. We will then measure perceived satisfaction and usability of the eHealth ecosystem. Finally, the cases at risk of emotional distress will be detected earlier than treatment as usual. Consequently, using new technologies, we will decrease the time to access appropriate psychosocial care.

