Considering previous results, the literature reviewed, and the objectives set forth, we hypothesized that two psychosocial treatments will improve emotional distress, demoralization, QoL, and medication adherence. Moreover, these improvements will be greater in patients with worse psychosocial results at baseline. For patients with a better baseline status, we expect the psychosocial interventions to exert a buffering effect despite disease progression. The eHealth ecosystem will obtain results equivalent to usual care for emotional distress, demoralization, QoL, and medication adherence. Spirituality at baseline, or its augmentation by psychosocial interventions, will predict better outcomes for emotional distress, demoralization, QoL, and medication adherence. Health education will improve markedly in the group allocated to the eHealth intervention. Compared with usual care, eHealth will have a superior cost-utility in terms of QALYs. Finally, users will be satisfied with the eHealth ecosystem and will perceive it as easy to use. The eHealth ecosystem will significantly improve the time to detection, intervention, and resolution of clinically significant psychosocial need compared to usual care.

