**Fig. 2 f0010:**
[figure not shown]
Stepped digital psychosocial intervention ICOnnecta’t.

The number of detected clinical cases: in the EG this will be obtained through the number of potential clinical cases recorded throughout treatment (VAS ≥6). In CG it will be obtained through the number of clinical cases recorded in the follow-up of face-to-face visits or if the patient reports a worsening by telephone and the visit is brought forward to confirm if it is a clinical case (VAS ≥6).

Waiting time to provide psychosocial intervention: In the EG, the time between the occurrence of a potential clinical case (VAS ≥ 6) and the start of psychosocial intervention will be assessed. The CG will assess the time between the face-to-face screening visit that confirms the clinical case and the next face-to-face visit.

Percentage of resolved psychosocial cases: in both groups it will be obtained through the number of clinical cases that are resolved.

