##### Level 2: campus: psychoeducation and health education

2.6.1.2

The ICOnnecta't Campus is an educational platform that can be accessed via Moodle. It allows patients to consult videos and online resources developed by health professionals and based on patient feedback. The campus therefore contains scientifically validated information related to the diagnosis and treatment of advanced oncological disease, organized into different thematic blocks that represent the usual challenges involved with an advanced oncological diagnosis (Graves et al., 2007). The key areas are as follows: (a) The medical aspects of lung cancer in 14 resources (i.e., common symptoms, medical treatments, and side effects; (b) Emotional aspects, with eight resources about emotional responses to diagnoses and treatment; (c) Personal relationships, with four resources addressed to family members and caregivers about the role of the family in treatment and how they can aid the patient during the process; d) Healthy habits, comprising 28 resources about exercise, healthy eating models, rest and self-care; and e) Spiritual, comprising three resources about spiritual worries, shared decision-making, and advance directives. The patient will remain at this level for two weeks. If distress does not decrease on the thermometer (score ≥ 6), a HADS and video consultation or phone call will be scheduled to assess the appropriateness (HADS score ≥ 10) of moving to the next level of care.

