##### Level 3: community psychosocial support

2.6.1.3

The service provides a safe online community where patients can anonymously share potential concerns related to the oncological process, resolve doubts and health issues, share experiences, or discuss issues related to the disease. This private social network contains several discussion forums related to advanced lung cancer and its possible implications, and they parallel the thematic blocks of ICOnnecta't Campus (level 2). It is supervised by a health psychologist who will provide a professional response with the support of other specialist members of the oncology team (e.g., psycho-oncologist, nurse, psychiatrist, and social worker). As in the previous level, the patient remains in this level for two weeks and is only advanced to level 4 if distress remains high (thermometer score ≥ 6), and a subsequent HADS score, and video or phone consultation indicate this is appropriate.

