##### Level 4: online group psychotherapy

2.6.1.4

In the final level, patients are offered online group psychotherapy led by a clinical psychologist with expertise in psycho-oncology. This comprises eight weekly 90-min sessions that use the meaning-centered group psychotherapy approach developed by Breitbart et al. (2015). Patients at this level remain on a waiting list until four to eight users become available for the group sessions.

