#### Treatment as usual - psychosocial face-to-face treatment

2.6.2

Patients in the control group will receive standard in-person psychosocial care delivered by a clinical psychologist. This will consist of an average of seven individual sessions, lasting 45–60 min each, with an inter-session spacing of 2–3 weeks. The clinical psychologist will provide the intervention based on individual meaning-centered psychotherapy for advanced cancer patients (Breitbart et al., 2012), aiming to help maintain or enhance the sense of meaning, peace, and purpose in the lives of patients with advanced cancer. Patients in this treatment arm will also have access to the educational materials of level 2 of the eHealth intervention, which will be provided in a freely accessible web portal for all patients and their families.

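### The waiting-time outcome names no level of care that stops the eHealth clock, so it cannot support the aim of faster access to appropriate care

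*Protocol article*

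**What the plan says.** All references are to the protocol article.

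- **Aim.** Section 1.1 states that "we will decrease the time to access appropriate psychosocial care", and the heading of section 2.5.2.3 repeats the idea of appropriate care. The hypotheses add that the eHealth ecosystem "will significantly improve the time to detection, intervention, and resolution of clinically significant psychosocial need compared to usual care".
- **eHealth clock.** Section 2.5.2.3: "the time between the occurrence of a potential clinical case (VAS ≥ 6) and the start of psychosocial intervention will be assessed". It does not say which level of care counts as the start.
- **Control clock.** The same section runs it from the face-to-face visit that confirms the case to the next face-to-face visit.
- **eHealth steps.** Section 2.6.1 describes the four levels together as one psychosocial intervention, which every patient enters at Level 1. A thermometer score of 6 or more leads to a call, and a confirmed case moves to Level 2 (section 2.6.1.1). For Level 2, "The patient will remain at this level for two weeks"; for Level 3, "the patient remains in this level for two weeks". For Level 4, "Patients at this level remain on a waiting list until four to eight users become available for the group sessions".
- **Control care.** Section 2.6.2 gives individual meaning-centered psychotherapy by a clinical psychologist, "with an inter-session spacing of 2–3 weeks". Control patients can also use the Level 2 educational materials.
- **Analysis.** Section 2.9 compares waiting time between the groups by Student t-test.

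**The concern.** The aim is about appropriate care, but the eHealth stop event is the start of an intervention at an unspecified level. In the control arm the clock stops at a visit which, by section 2.6.2, is with the psychologist who delivers the therapy. In the eHealth arm an assessment call or access to videos would satisfy the wording. The videos are open to control patients too, yet do not stop their clock.

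At stake is the hypothesis of faster access. A difference between the arms could reflect how soon a first contact or first step occurs and be reported as faster access to appropriate care. For patients who go on to need Level 4, that report could hide a longer route to psychotherapy.

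**Working it through.** The plan gives no expected waiting time, so there is no figure of its own to reproduce. The check adds up the stated intervals.

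**Inputs**
- Level 2 stay: 14 days (2.6.1.2).
- Level 3 stay: 14 days (2.6.1.3).
- Level 4 queue: until four to eight users are available, with no upper limit stated (2.6.1.4).
- Control session spacing: 14 to 21 days (2.6.2).

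**Step 1: eHealth, distress persisting.** The shortest time from entering Level 2 to joining the Level 4 queue is 14 + 14 = 28 days. The calls between steps and the queue come on top; the article gives no duration for either.

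**Step 2: control.** Taking the stated spacing as the gap between the confirming visit and the next visit, the wait is 14 to 21 days.

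**Step 3: difference.** 28 − 21 = 7 days and 28 − 14 = 14 days. The eHealth route to therapist-led psychotherapy is thus at least 7 to 14 days longer for these patients, before any queue. Both counts begin once a professional has confirmed the case, so this step does not depend on the unequal clock starts. The end points are similar in kind: group and individual meaning-centered psychotherapy.

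**Step 4: what the outcome records under each reading of the stop event**

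| Reading | Consequence for a patient who reaches Level 4 |
|---|---|
| Stops at the Level 1 call or at Level 2 entry | At least 28 days plus the queue are left out |
| A later score of 6 or more opens a new case | The queue may be counted, but the clock restarts, so the 28 days never appear as part of one wait |
| Stops only at Level 4 | A patient who dies or finishes in the queue has no observed wait to enter into a t-test |

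Under none of these does the outcome give the full time to therapy for all such patients.

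**Step 5: size of the queue.** This cannot be computed from the article. For illustration only, assume that 10% to 30% of the 76 eHealth patients reach Level 4, arriving evenly over 12 to 36 months, that groups form at four, and that only trial patients fill them. With gap g between arrivals, the four waits are 3g, 2g, g and 0, a mean of 1.5g.
- 30% over 12 months: 76 × 0.30 = 22.8 patients; g = 12 × 30.4 / 22.8 = 16 days; mean 24 days.
- 10% over 36 months: 7.6 patients; g = 36 × 30.4 / 7.6 = 144 days; mean 216 days.

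This ignores deaths, dropout and the 9-month limit, and the waits shrink if users from outside the trial join the groups. The point rests on Steps 1 to 4.

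**The case against.** - **The stop event is undefined, not wrongly defined.** A reader might infer that the clock stops at the Level 1 call or the videos and that the Level 4 queue is never counted. The article does not say so. Potential cases are recorded throughout treatment, so a high score at Level 3 might open a new clock that runs to Level 4. This stands. An unseen analysis plan might also name the event. But the article itself sets out the measure in both arms and the test, and what it sets out does not match its aim.
- **Stepped care starts low by design.** For patients whose distress settles at Level 2 or 3, that level is the appropriate care, and nobody has judged them to need Level 4 when the clock starts. This stands, and limits the point to those who reach Level 4. It also rules out timing everyone to the level finally reached, which would group patients by later non-response and count delivered care as waiting.
- **Other routes exist.** Section 2.6.1 allows referral to psycho-oncology, psychiatry or social work, and a psychologist follows each patient. Some patients may therefore reach individual care sooner, and one for whom no group forms is not necessarily without care.
- **The clock starts differ in the other direction.** The eHealth clock starts at an unconfirmed case and the control clock at a confirmed one, so control detection delay goes uncounted. This favours control.
- **Some information is collected.** The article reports the percentage of resolved cases and the numbers reaching each step. Neither gives the Level 4 wait.

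**Conclusion.** The point holds in limited form. As stated, the waiting-time outcome cannot support a conclusion about access to appropriate care: the eHealth stop event is open, it is not matched to the control stop event, and no stated measure reports the Level 4 wait. For patients who reach Level 4, the stated intervals give at least 28 days from Level 2 entry plus an unlimited queue, against 14 to 21 days between control sessions. This assumes that the control spacing applies after a confirming visit and that the patient is not referred earlier.

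Two stronger readings are not supported. One is that the outcome is biased towards eHealth overall: the share reaching Level 4 is not given and the unequal clock starts work the other way, so the net sign is not fixed. The other is that a particular proportion of Level 4 patients would never join a group: any such figure depends on assumed accrual, need and survival.

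This is a secondary outcome. The HADS non-inferiority test and the sample size do not depend on it.

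**What to change.** These changes concern measurement only, not the steps or the care given.

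1. Name the event that stops the eHealth clock, and label the present measure *time to first contact or step*.
2. Add, in both arms and from a confirmed case, the time to the first psychologist-delivered therapy session after confirmation. For Level 4 this is the first group session, including time on the list; sessions reached by referral count. State in advance that an assessment call is not a therapy session.
3. Analyse the added measure by cumulative incidence, so that death or end of follow-up without a session is accounted for, instead of a t-test on observed waits. Show cases that resolve without a session separately, since stepped care intends some of these.
4. Report descriptively the Level 4 list wait and the number who never start a group.

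Starting from a confirmed case leaves detection delay out in both arms, so time to detection still needs its own report. The cost is some wording and a few more dates to record: confirmation, joining the list, first session. The eHealth waiting time may look less favourable as a result.

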##### Early detection of patients at risk of emotional distress and time to receive appropriate psychosocial care

2.5.2.3

Well-being - emotional discomfort screening: it will be evaluated through an emotional state thermometer with a response system in VAS format, which will be scheduled weekly on the ICOnnecta't platform (see Fig. 2).

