##### Level 1: screening and monitoring

2.6.1.1

Screening of potential emotional distress and monitoring of physical symptoms through a mobile application (ICOnnecta't App). Patients can spontaneously communicate their mood through a VAS emotional thermometer. In addition, a health psychologist will program a weekly assessment with the same thermometer, with a score ≥ 6 (10 indicating maximum distress) triggering a video consultation or phone call to assess the distress and explore any specific psychosocial needs. These sessions are also intended to accompany the patient throughout their cancer journey. Before a session, patients complete the HADS, and if both the HADS (≥ 10) and the psychologist's impression confirm clinically significant distress, the patient will be escalated to the next level. This adaptation of a stepped-care program used in oncology will be followed for escalation to the subsequent levels (Jansen et al., 2017).

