### Planned statistical analysis

2.9

Descriptive analyses will be performed using Student t or chi-squared tests, as appropriate. This will include assessment of sociodemographic and clinical variables at baseline, together with any pre-treatment differences between groups. Intention-to-treat analyses will then be performed through multilevel linear models to compare both groups on each primary outcome: emotional distress (HADS), demoralization (DS-II), QoL (FACT-L), and medication adherence (ARMS-e).

The modeling process will be parsimonious and guided by fit indexes, starting with a model using the time and type of therapy as fixed predictors. Then, random effects will be tested, and the interaction between time and type of therapy, the eHealth step reached, symptomatology (ESAS-r), and spirituality (FACIT-Sp) will be progressively entered as predictors. The estimation method will be maximum likelihood. Effect sizes (Hedges' g) will be reported for the primary outcomes and non-inferiority will be assessed for the HADS by comparing the means of both groups at T2 and T3. Additional multilevel linear models will be run to assess changes in health education (VAS) between groups, according to the same procedures. As for the cost-utility analyses, the EQ-5D will be used to compute the QALYs together with associated costs for medical care, psychotropics, sick leave, professional salaries, infrastructure, and transportation.

Descriptive analyses will also be conducted for platform's satisfaction and usability (VAS), as well as for participants reaching each step in the eHealth group. Mean differences in the number of clinical cases detected (according to the emotional thermometer), waiting time to provide care, and number of clinical cases solved will then be compared between groups by Student *t*-tests. For the reporting of results, 95 % confidence intervals will be provided. Analyses will be performed using IBM SPSS version 24 (IBM Corp., Armonk, NY, USA) and R software, with support provided by the biostatistics department of IDIBELL.

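### Detected cases and waiting time are measured differently in the two arms, and resolved cases change from a percentage to a number, so these between-arm comparisons cannot be interpreted

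*Protocol article*

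**What the plan says.** Section 2.5.2.3 sets three measures.

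- **Cases detected.** In the eHealth arm (EG), "in the EG this will be obtained through the number of potential clinical cases recorded throughout treatment". The instrument is an emotional thermometer, "which will be scheduled weekly on the ICOnnecta't platform", and section 2.6.1.1 adds: "Patients can spontaneously communicate their mood through a VAS emotional thermometer". For the control arm (CG): "In CG it will be obtained through the number of clinical cases recorded in the follow-up of face-to-face visits", or when a telephone report of worsening brings a visit forward and that visit confirms the case. Both arms use VAS ≥6. Section 2.6.2 gives control patients seven sessions on average, with an "inter-session spacing of 2–3 weeks".
- **Waiting time.** In the EG it runs from the unconfirmed case to the start of psychosocial intervention. For control: "The CG will assess the time between the face-to-face screening visit that confirms the clinical case and the next face-to-face visit".
- **Resolved cases.** One sentence covers both arms, under a label that calls the measure a percentage.

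Section 2.9 compares the mean number of detected cases between arms, and says that "waiting time to provide care, and number of clinical cases solved will then be compared between groups by Student" t-tests. Section 1.1 states the hypothesis that these measures serve: "The eHealth ecosystem will significantly improve the time to detection, intervention, and resolution of clinically significant psychosocial need compared to usual care".

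**The concern.** A between-arm difference means something only if the same event is counted, with the same chance of being seen, and timed from and to the same points. Here the EG counts a single screening score without the confirmation step that the protocol itself describes in 2.6.1.1 (HADS ≥10 plus the psychologist's impression). The CG counts what is recorded or confirmed at a visit. The opportunities to be counted also differ, and the two clocks start and stop at different kinds of event.

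At stake is a stated aim and a superiority hypothesis on detection, access to care and resolution. If the plan is followed as written, a significant t-test could reflect the screening schedule and the clock definitions, and nothing in the data would show how much.

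**Working it through.** The plan gives no figure of its own for these outcomes, so there is none to reproduce. The check sets out the schedules, then asks what the stated counting rules give when both arms have the same distress.

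**1. Opportunities to be counted.** EG: 9 months × 52/12 = 39 weekly readings, plus spontaneous ones. CG: seven visits have 6 gaps; 6 × 2 = 12 weeks and 6 × 3 = 18 weeks, so an average course ends at about week 12–18 of 39 if it starts at once. The ratio of checks is 39/7 = 5.6. This is not the ratio of cases, because an episode lasting several weeks gives many positive readings but is one case.

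**2. Case counts with no true difference.** Simulation with the following assumptions, none of them from the protocol unless stated:

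- Same process in both arms: one episode onset per 13 distress-free weeks, mean duration 2, 4 or 8 weeks.
- An episode counts once if a check falls inside it.
- CG visits 2 or 3 weeks apart (2.6.2), either seven in all or continuing for 39 weeks.
- Missed CG episodes phoned in never, or 30% of the time.
- 57 evaluable patients per arm: 76 × (1 − 0.25), from section 2.7.
- Chance of significance in favour of EG = Φ(difference/SE − 1.96). With unbiased counting this would be 2.5%.

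| CG visits | Missed episodes phoned in | EG/CG case ratio | Chance the test favours EG |
|---|---|---|---|
| Seven | none | 2.1–3.7 | about 100% |
| Seven | 30% | 1.5–1.8 | 95–100% |
| All 9 months | none | 1.07–1.6 | 10–92% |
| All 9 months | 30% | 1.03–1.2 | 5–33% |

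Example: mean episode 4 weeks, visits 2 weeks apart, seven visits, no phone-in gives 2.05 cases per patient in the EG and 0.65 in the CG, a ratio of 3.17 before rounding. The simulation gives the EG no spontaneous readings and no scores that would fail confirmation; either would raise its count further.

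**3. Waiting time.** Two effects pull in opposite directions.

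- *Start.* In the simulation with visits throughout, the mean lag from onset to the detecting check was 3.2–3.4 days in the EG and 5.8–9.7 days in the CG. Neither clock includes it, but the CG loses more: 5.8 − 3.2 = 2.6 days up to 9.7 − 3.4 = 6.3 days. For a phoned-in case, the time from the call to the visit is also left out. This favours CG.
- *Stop.* The CG clock ends at the next visit, which the planned spacing puts at about 14–21 days (midpoint 17.5), even if the confirming visit was itself a session. This favours EG.

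To see how easily the stop point alone gives significance, take CG waits uniform on 14–21 days (SD 7/√12 = 2.02) and assume an EG mean wait of 10 days, SD 7. With 10 cases per arm, (17.5 − 10)/√(7²/10 + 2.02²/10) − 1.96 = 1.29, so power is 90%; with 30 cases it is about 100%. An assumed EG wait of 14 days gives 33% (10 cases) to 75% (30 cases). Such a result would mostly compare an EG response time with a visit interval.

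**4. Resolved cases.** Number solved = cases detected × share resolved. If the share is equal in both arms, the ratio of numbers solved equals the ratio of cases detected, so the number in 2.9 carries the whole multiplier in the table. The percentage in 2.5.2.3 would not carry it directly, although its denominator is still formed by different rules.

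**5. Match to the hypothesis.** Section 1.1 speaks of time to detection and time to resolution. Section 2.5.2.3 defines a count, a waiting time and a percentage, so neither of those two times has a measure.

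**The case against.** The best defence is that weekly monitoring is Level 1 of the intervention. Finding more cases sooner through screening is the mechanism under test, so a higher count may be a real benefit. That stands as far as it goes: a true gain is possible. But these measures cannot separate it from ascertainment, because the extra EG cases are unconfirmed and no common set of cases exists against which detection could be judged.

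It is also fair that both arms share the VAS ≥6 cut-off, that control visits can be prompted by telephone, and that seven sessions is an average. These points shrink the imbalance, as the lower rows of the table show, but do not remove it.

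A reader might infer several stronger things that the document does not support:

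- *That an eHealth advantage is built into all three measures.* For waiting time the effects oppose each other and the net direction is unknown.
- *That resolution is defined differently by arm.* One sentence serves both; the fault is percentage against number.
- *That the count is inflated 5.6-fold.* That treats neighbouring weekly scores as independent new cases and ignores phone-in.
- *That deaths and unresolved cases are mishandled.* That may be settled in an analysis plan that is not shown.

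**Conclusion.** The point holds as a defect of comparability in secondary outcomes. It is not missing detail: applying the stated rules exactly gives comparisons that cannot be interpreted.

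For detected cases the direction is clear, but the size depends on assumptions about episode length, phone-in and how long control visits continue: from 1.03 to 3.7 times with no true difference. For waiting time the difference cannot be read in either direction. For resolution, 2.5.2.3 and 2.9 disagree, and the number in 2.9 inherits the detection imbalance. The choice of a t-test is the lesser problem; another test on the same definitions would not help.

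A reader might conclude that the trial's main result is compromised. It is not: the HADS non-inferiority comparison and its sample size do not use these measures. Severity: should-fix.

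**What to change.** For the between-arm comparison, use what both arms already provide on one schedule, the HADS sent through REDCap (sections 2.4 and 2.5.1):

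- **Case:** HADS ≥10 at T0, T1 or T2, in either arm. This cut-off is already in 2.5.1 and 2.6.1.1. Exclude cases at T3, which have no next assessment.
- **Detection:** share of those cases that the care team recorded as a case (not a thermometer score alone) before the next assessment.
- **Waiting time:** from that HADS date to the first recorded psychosocial contact, the same clock in both arms, analysed as time-to-event.
- **Resolution:** share with HADS <10 at the next assessment, as a risk difference with 95% CI. Make 2.5.2.3 and 2.9 agree on this.
- **Thermometer counts and thermometer-to-care times:** report as EG-only process data and drop their between-arm t-tests.
- **Section 1.1:** limit the claim on time to detection to what these measures can show.

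The cost is a change to outcome definitions and analysis wording; the HADS is already collected and care does not change. There are three downsides to state. A 3-monthly HADS misses short episodes and cannot time detection between assessments. Planned contact schedules still differ by arm, which must be said when waiting time is interpreted. Cases at T1 and T2 arise after randomisation, so the T0 cases are best also shown separately.
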